## 3. Results

No solid results of the ongoing study are given; only the status of recruitment at the time of writing is reported. In total, 167 patients with IBD have been enrolled with detailed phenotyping and bio-sampling.

### 3.1. Characteristics of the IBD Study Population

The main characteristics of the IBD study population are depicted in Supplementary Table S1. Enrollment is still in progress, and the end of follow-up is estimated to be by the end of 2027. During the last 3–6 months of the project, multi-omics evaluation and analysis will be performed. At that time, the full data analysis will be shared.

### 3.2. Characteristics of the Control Population

Table 3 reports the basal characteristics of the control population enrolled in the study CV PREVITAL. The enrollment of this cohort is complete, and all subjects underwent evaluation of their CV risk score and provided blood samples at baseline to evaluate total cholesterol and its fractions, fasting glucose, glycate hemoglobin, triglycerides, homocysteine, and C reactive protein. In addition, bio-samples were collected for further possible multi-omics evaluation and carotid intima-media thickness (IMT) evaluation by Doppler ultrasound. By applying the propensity score from this cohort, an age- and gender-matched control population will be selected for comparison with the IBD cohort.

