
The control cohort will be that of the CV-PREVITAL trial (a multicenter, prospective, randomized, controlled, open-label interventional trial—NCT05339841) designed to compare the effectiveness of an educational and motivational mobile health (mHealth) intervention versus usual care in reducing CV risk. The Cardiology Unit of IRCC Policlinico San Donato has already enrolled 1109 healthy individuals in this trial. These participants, who were free from known CVDs at baseline, have already completed a 1-year follow-up and are still under cardiological evaluation to monitor their CV health over time. The control group for the IBD cohort, matched for age and sex, will be extrapolated from this population.

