### 2.5. Statistical Analysis

In this study, a combination of descriptive and inferential statistical methods will be required to ensure robust analysis. For descriptive statistics of the key characteristics of the study (CD, UC, and matched controls), we used the mean and standard deviation (for continuous variables such as age and BMI), median and interquartile range (for skewed variables), and counts and percentages (for categorical variables, such as sex and smoking status). To check the balance between the groups, the standardized mean differences (SMDs) will assess the balance of covariates between the groups. An SMD < 0.1 typically indicates good balance. *t*-tests or Mann–Whitney U tests (depending on normality) for continuous variables will compare means or medians across groups. Chi-square tests or Fisher’s exact tests for categorical variables will compare proportions across groups. In view of the evaluation of the outcome of MACEs, we will use Kaplan–Meier survival analysis to estimate the time to the cardiovascular event, stratified by subgroups. In addition, a Cox proportional hazard regression will allow for evaluation of the hazard ratio (HR) of MACEs while adjusting for confounders. The log-rank test will compare the survival curves between the different groups. We will also apply a multivariate logistic regression evaluating the outcome as binary (e.g., MACEs occurring vs. not occurring during the study period). To ensure the robustness of our findings, sensitivity analyses, such as propensity score matching sensitivity may be performed. Because missing data is common in prospective studies, multiple imputation methods will be used to handle missing data in covariates or outcomes.

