A multidisciplinary approach is essential for appropriately addressing the interplay between IBD and cardiovascular risk. Beyond early detection and effective treatment, secondary prevention should be prioritized. In this context, recommendations from the American Heart Association support strategies to mitigate cardiovascular risk in patients with IBD, emphasizing the maintenance of disease remission as a key factor in reducing atherosclerotic cardiovascular disease (ASCVD) risk [11]. These guidelines also underscore the need for aggressive control of modifiable risk factors, including routine screening of blood pressure, blood glucose, lipid profiles, and promotion of healthier lifestyle choices. Moreover, there is a strong rationale for adopting personalized prevention strategies in IBD care. Clinicians can tailor interventions by identifying individuals at greater risk of cardiovascular complications, thereby facilitating informed, shared decision-making [11].

Several limitations still exist in fully understanding the IBD–CVD relationship, particularly with regard to therapeutic effects, biological pathways, and the availability of laboratory tools, such as biomarkers, that could help anticipate cardiovascular risk and pathogenesis.

Traditional risk calculators, such as SCORE2, likely underestimate CVD risk in patients with IBD. As seen in rheumatoid arthritis, a correction factor of 1.5 is recommended to account for the persistent inflammatory burden; a similar adjustment may be warranted in patients with IBD [18].

Our study will provide a comprehensive analysis of how disease activity, treatment regimens, and multi-omics profiles influence cardiovascular risk. This approach may help identify common risk pathways and open new prevention and management avenues. At the moment, we have only reported the status of recruitment in Section 3. The control population inclusion, derived from the PREVITAL study, is complete and will be used for gender- and age-matched comparison by applying the propensity score methodology. In contrast, the enrollment of the patients with IBD will be completed by the end of 2025, and after 2 years of follow-up, multi-omics evaluation will be performed and analyzed.

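### Propensity-score matching both selects the main controls and is listed as an optional sensitivity analysis; the primary baseline-risk comparison needs one stated rule, best met by direct matching on sex and age

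*Protocol article*

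**What the plan says.** The protocol article describes the choice of controls in four places.

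- **Section 2.1** names the matching variables but no tool: "The control group for the IBD cohort, matched for age and sex, will be extrapolated from this population". The primary objective in Section 2.4 likewise compares baseline CVD risk with a cohort matched on age and gender.
- **Section 3.2** names the tool: "By applying the propensity score from this cohort, an age- and gender-matched control population will be selected for comparison with the IBD cohort".
- **Section 4** says the same of the control population, which "will be used for gender- and age-matched comparison by applying the propensity score methodology".
- **Section 2.5**, the statistical section, gives the technique a different role: "sensitivity analyses, such as propensity score matching sensitivity may be performed".

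Section 2.5 also plans a balance check: "the standardized mean differences (SMDs) will assess the balance of covariates between the groups", followed by "An SMD < 0.1 typically indicates good balance". The covariates to be checked are not named. Age, BMI, sex and smoking status appear just before, as examples of variables to be described.

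Baseline risk is measured with SCORE2 (Sections 2.1, 2.3 and 5).

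**The concern.** One procedure cannot both select the primary control group and be an optional check on that selection, unless the two versions differ in their covariates. If both use age and sex, the sensitivity analysis largely repeats the main one. If they differ, the article does not say how.

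The role of the score matters more here than in most cohort studies, because the primary outcome is itself a baseline risk score. Two things are at stake.

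1. **Quality of the match.** A score on age and sex is a single number. An older patient of one sex and a younger patient of the other can share the same value, so close matching on the score is not close matching on age and sex.
2. **What is being estimated.** Matching on age and sex leaves the whole remaining difference in baseline risk visible. Matching also on factors that feed the risk score takes part or all of that difference away. Propensity scores are commonly used to balance many covariates, so an analyst working from Sections 3.2 and 4 could add such factors unless told not to.

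**Working it through.** **1. The plan's own figure.** No stated figure depends on how controls are matched. The one tied to the matched sample is 80% power for a hazard ratio of 2.5 with 300 per group and 1% per year in controls (Section 2.5). Over 4 years, p₁ = 1 − exp(−0.04) = 0.0392 and p₂ = 1 − exp(−0.10) = 0.0952. Then Cohen's h = 2·arcsin√p₂ − 2·arcsin√p₁ ≈ 0.2285, and power = Φ(h·√(300/2) − 1.96) = 79.9%. The figure reproduces, and the present point does not touch it.

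**2. The texts side by side.**

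| Section | Matching variables named | Tool | Role |
|---|---|---|---|
| 2.1, 2.4 | age, sex | none named | main comparison |
| 3.2, 4 | age, gender | propensity score | main comparison |
| 2.5 | none | propensity-score matching | optional sensitivity analysis |

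Sections 2.1/2.4 and 3.2/4 are compatible: same variables, with the tool added. The clash is between 3.2/4 and 2.5.

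**3. What a score on age and sex does.** Illustrative simulation, 400 runs.
- From the documents: 1109 controls, 492 men aged 56.9 ± 6.5 and 617 women aged 55.1 ± 6.2 (Table 3); 300 IBD patients (Section 2.5).
- Assumed: IBD patients 50% male; smoking 25% vs 15%; a blood-pressure/lipid index 0.2 SD worse in IBD; log risk = 0.08·age + 0.5·male + 0.6·smoking + 0.25·index.
- True difference at equal age and sex: 0.6 × 0.10 + 0.25 × 0.2 = 0.11.
- Score match: age, age² and sex; greedy 1:1 nearest neighbour, caliper 0.2 SD of the logit.
- Direct match: exact sex, nearest age within 2 years.

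| Assumed IBD age | Method | Pairs | Opposite sex | Mean difference | SD over runs |
|---|---|---|---|---|---|
| 54 ± 7 | score | 295 | 35% | 0.122 | 0.0362 |
| 54 ± 7 | direct | 296 | 0% | 0.111 | 0.0268 |
| 45 ± 12 | score | 192 | 41% | 0.115 | 0.0496 |
| 45 ± 12 | direct | 192 | 0% | 0.105 | 0.0334 |

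Both methods are close to unbiased and keep about the same number of pairs. Direct matching cuts the SD by 1 − 0.0268/0.0362 = 26% and 1 − 0.0334/0.0496 = 33%. With age entered only linearly, the opposite-sex share was 41% and 50%, and the gain 21% and 19%. Separately coded runs on similar inputs gave 36–40% opposite-sex pairs and a gain of about 25–45%.

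The opposite-sex share is unsurprising. If the score carried no information on sex, pairing would be random on sex: 0.5 × 617/1109 + 0.5 × 492/1109 = 50%.

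**4. What happens if risk factors enter the score.** In a separate illustrative model (200 runs), the risk index depends on age, sex and three risk factors. Each factor has weight 0.4 and is shifted by 0.3 SD in IBD. The true difference is 3 × 0.4 × 0.3 = 0.36.

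| Score contains | Difference after matching | Share removed |
|---|---|---|
| age, sex | 0.37 | none |
| plus one risk factor | 0.23 (theory 2 × 0.4 × 0.3 = 0.24) | (0.36 − 0.23)/0.36 = 36% |
| plus all three | 0.01 | (0.36 − 0.01)/0.36 = 97% |

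**5. Reach of the control pool.** With age 55.9 ± 6.5 and a normal approximation, the share under 40 is Φ((40 − 55.9)/6.5) = Φ(−2.45) = 0.7%, or about 8 of 1109.

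**The case against.** **The score is only the tool.** Sections 3.2 and 4 name age and gender as what is matched and the propensity score as the means. This stands: a reader might infer three rival definitions of the control group, but Sections 2.1, 2.4, 3.2 and 4 agree on the variables.

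**Section 2.5 may mean something else.** Its wording could refer to varying the propensity match itself. It also follows the MACE methods, so it may concern MACE alone. Either reading is possible and would soften the clash. Neither is stated, and the primary rule would still need to be.

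**The documents do not say that the primary difference is matched away.** A reader might infer this from the mention of a propensity score. No section puts smoking, BMI, blood pressure or lipids into it, and a score on age and sex leaves the difference essentially intact. The near-zero result in step 4 also follows by construction, because the index there has no other determinants; with one factor of three the loss is partial. A covariate list absent from a journal article may stand in the full protocol or analysis plan and is no finding by itself.

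**The SMD check does not force groups to be equal.** A reader might take the 0.1 threshold as a target for BMI and smoking. It is a diagnostic with no rule to re-match or discard, and the same paragraph goes on to test group differences.

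**Matched pairs are not promised.** The article speaks of a matched cohort, population or group. So opposite-sex pairs do not contradict the text. They do cost precision, and they fall short of what many readers will understand by age- and sex-matched controls.

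**Conclusion.** The inconsistency is real but narrow: propensity-score matching is the main selection method in Sections 3.2 and 4 and an optional sensitivity analysis in Section 2.5. These agree only if the scores use different covariates or Section 2.5 means something it does not say.

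A score on age and sex would not bias the primary comparison materially. It would leave roughly 36–40% of pairs of opposite sex. Direct matching would reduce the SD of the primary difference by about a fifth to a third, and by up to 45% in some runs, with no loss of pairs.

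The loss of the SCORE2 difference is conditional on risk factors entering the score, which the article does not state. It is a risk to close off, not a demonstrated error.

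The simulations rest on assumed IBD ages, sex mix, risk-factor differences and coefficients. They show direction and are not estimates for this trial.

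**What to change.** State one rule for the primary comparison, in the same words in Sections 2.1, 2.5, 3.2 and 4:

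- Match exactly on sex and within a fixed age caliper (for example ± 2 years), with no cardiovascular risk factor in the matching.
- Use SMD < 0.1 as an acceptance check for age and sex only. Report the SMDs of BMI, smoking and other risk factors as results, not as failures of balance.
- Keep any propensity score that includes risk factors for a separately labelled sensitivity analysis of MACE, and say so in Section 2.5.
- Report how many IBD patients have no control within the caliper, with their ages.

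The cost is wording and a simple matching specification. The control pool is already enrolled, and the article describes the matching as still to come.

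The drawback is the age range of the pool. With about 8 controls under 40 on a normal approximation, many of the youngest IBD patients may go unmatched, although the article names them as a group of special interest. With IBD patients assumed to be 45 ± 12 years old, 300 − 192 = 108 were unmatched. The calipered propensity match left the same number, so the limit lies in the pool and not in the proposed rule.

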## 4. Discussion

The precise mechanisms responsible for the development of cardiovascular events in individuals with inflammatory bowel disease (IBD) remain incompletely defined [7,8,12]. Additional studies are needed to unravel the intricate relationship between systemic inflammation, immune system disturbances, and the onset of cardiovascular disease (CVD) in this population [8]. IBD represents a heterogeneous group of conditions with diverse clinical presentations and trajectories [3,4]. However, most existing research tends to treat IBD as a unified entity, often overlooking possible distinctions in CVD risk between ulcerative colitis (UC) and Crohn’s disease (CD), or across varying levels of disease severity. Further investigation is essential to better characterize these differences and to enable more tailored preventive and therapeutic strategies. Additionally, much of the current evidence is derived from observational or retrospective studies, limiting the ability to draw definitive causal inferences regarding CVD development in this setting (see Appendix A).

At present, there are no specific, validated guidelines for cardiovascular risk assessment in patients with IBD. Many IBD patients are younger adults who fall outside the demographic typically assessed by conventional cardiovascular risk calculators. Nevertheless, the 2019 guidelines from the European Society of Cardiology recognized IBD—alongside conditions such as cancer therapies, rheumatoid arthritis, and systemic lupus erythematosus—as requiring heightened vigilance in screening, counseling, and management for atherosclerotic disease [79]. Similarly, guidance from the European Alliance of Associations for Rheumatology highlights the importance of monitoring inflammatory activity using biomarkers, a principle that may be equally relevant to IBD populations [18].

A multidisciplinary approach is essential for appropriately addressing the interplay between IBD and cardiovascular risk. Beyond early detection and effective treatment, secondary prevention should be prioritized. In this context, recommendations from the American Heart Association support strategies to mitigate cardiovascular risk in patients with IBD, emphasizing the maintenance of disease remission as a key factor in reducing atherosclerotic cardiovascular disease (ASCVD) risk [11]. These guidelines also underscore the need for aggressive control of modifiable risk factors, including routine screening of blood pressure, blood glucose, lipid profiles, and promotion of healthier lifestyle choices. Moreover, there is a strong rationale for adopting personalized prevention strategies in IBD care. Clinicians can tailor interventions by identifying individuals at greater risk of cardiovascular complications, thereby facilitating informed, shared decision-making [11].

Several limitations still exist in fully understanding the IBD–CVD relationship, particularly with regard to therapeutic effects, biological pathways, and the availability of laboratory tools, such as biomarkers, that could help anticipate cardiovascular risk and pathogenesis.

Traditional risk calculators, such as SCORE2, likely underestimate CVD risk in patients with IBD. As seen in rheumatoid arthritis, a correction factor of 1.5 is recommended to account for the persistent inflammatory burden; a similar adjustment may be warranted in patients with IBD [18].

Our study will provide a comprehensive analysis of how disease activity, treatment regimens, and multi-omics profiles influence cardiovascular risk. This approach may help identify common risk pathways and open new prevention and management avenues. At the moment, we have only reported the status of recruitment in Section 3. The control population inclusion, derived from the PREVITAL study, is complete and will be used for gender- and age-matched comparison by applying the propensity score methodology. In contrast, the enrollment of the patients with IBD will be completed by the end of 2025, and after 2 years of follow-up, multi-omics evaluation will be performed and analyzed.

In Italy, there are currently an estimated 250,000 to 300,000 patients with IBD, with projections indicating a possible doubling over the next decade [1]. This trend will inevitably place greater pressure on the national healthcare system. A major strength of our study is its structured approach—applying standard care protocols and monitoring both clinical disease features and lifestyle data over a 5-year period (3 years retrospectively, 2 years prospectively). In addition, we will compare this cohort to a well-matched, rigorously followed control population. Multi-omics analysis will be used to identify potential biomarkers associated with increased cardiovascular risk.

Upon completion of the study, we aim to propose an IBD-specific correction factor to enhance the accuracy of existing CV risk scoring systems. This will be particularly valuable for younger patients—especially those under 40 years—who are not adequately captured by current tools.

Indeed, this subgroup appears to show a more pronounced disparity in MACE incidence compared to the general population. Notably, this will be the first prospective investigation in Italy specifically designed to evaluate CVD risk in patients with IBD and one of only a few worldwide [43]. The findings of this study will offer important insights to clinicians, researchers, and policymakers, contributing to more informed strategies to reduce cardiovascular morbidity and mortality in this vulnerable group.

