## Abstract

**Background/Objectives**: The global burden of inflammatory bowel diseases (IBDs) continues to rise, with up to 50% of patients experiencing extraintestinal manifestations. Cardiovascular diseases (CVDs) are of particular concern, ranking as the second leading cause of mortality in this population. Despite a comparatively lower prevalence of traditional cardiovascular (CV) risk factors, the persistent inflammatory milieu and immune dysregulation inherent to IBD may contribute to heightened CVD risk. In this study, following a review of the current literature, an ongoing prospective trial designed to clarify CV risk profiles in IBD patients is detailed. **Methods**: A cohort of patients with IBD is being enrolled for comprehensive baseline evaluation of CV risk factors, lifestyle metrics, and disease characteristics. The incidence of major adverse cardiovascular events (MACEs) will be tracked and contrasted with a gender- and age-matched non-IBD cohort over a 2-year follow-up period. In cases of MACE occurrence, a multi-omics analysis—including genomic, proteomic, transcriptomic, and microbiome profiling—will be performed, along with a parallel evaluation in matched IBD controls without MACE. An artificial intelligence (AI) framework will support the analysis of this complex dataset. **Results**: To date, over 150 patients with IBD have been enrolled, and detailed phenotypic data and biological samples have been collected. **Conclusions**: We aim to introduce an IBD-specific correction factor for existing CV risk scores upon study completion. This is particularly relevant for individuals under 40 years of age, who are often inadequately assessed by current risk stratification models

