### 2.4. Objectives of the Study

The primary objective of the study will be to evaluate the basal CVD risk in our IBD population compared with the age- and gender-matched cohort of non-IBD patients.

The secondary objectives will be as follows:–Correlation of the basal CVD risk with multi-omics biomarkers, disease activity, lifestyle (i.e., diet, smoking) and therapy;–To evaluate the occurrence of MACEs at the end of follow-up in the patients with IBD and control populations;–To investigate the possible correlation between high CVD risk and MACE occurrence with multi-omics findings;–To identify possible biomarkers of increased CVD risk compared with the control population;–To establish possible correction factors to apply to the standard traditional CVD risk score to incorporate the IBD inflammatory burden.

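### The closed control pool holds almost nobody under 40, so young IBD patients will be dropped or paired with older controls, and a correction factor used under 40 would be extrapolated

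*Protocol article*

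**What the plan says.** The primary objective (section 2.4) is to "evaluate the basal CVD risk in our IBD population compared with the age- and gender-matched cohort of non-IBD patients". MACE occurrence in both groups and possible correction factors for the standard risk score are secondary objectives.

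There is one source of controls. Section 2.1 says that the Cardiology Unit "has already enrolled 1109 healthy individuals in this trial" (CV-PREVITAL) and that "The control group for the IBD cohort, matched for age and sex, will be extrapolated from this population". Section 3.2 adds that "The enrollment of this cohort is complete" and that, using a propensity score, "an age- and gender-matched control population will be selected for comparison with the IBD cohort". Table 3 gives the age of this pool as 55.9 ± 6.5 years overall (N = 1109), 56.9 ± 6.5 in men (N = 492) and 55.1 ± 6.2 in women (N = 617). No age range is printed.

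On the IBD side, the Conclusions speak of all consecutive patients, and the article states no lower age limit. The Discussion remarks that "Many IBD patients are younger adults who fall outside the demographic typically assessed by conventional cardiovascular risk calculators". The Abstract says of the planned correction factor: "This is particularly relevant for individuals under 40 years of age, who are often inadequately assessed by current risk stratification models". The Discussion repeats the emphasis ("especially those under 40 years—who are not adequately captured by current tools") and describes the control population as well matched.

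**The concern.** Matching can only use people who are in the pool. A pool centred near 56 with an SD of 6.5 years has very few members in the age group that the article singles out, and with enrolment closed none will be added.

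The main stake is the primary comparison. Age is among the traditional cardiovascular risk factors in the article's own Table 1. If a young patient is paired with a much older control, the control carries more baseline risk and a higher expected event rate, and the IBD group looks safer by comparison. That runs against the study hypothesis and could hide a real excess. If young patients are dropped instead, the comparison stays fair but describes a narrower and older population than the article suggests, with fewer than the planned 300 pairs.

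The second stake is the correction factor. Whatever value is found at older ages, the study has almost no non-IBD data with which to check it below 40.

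**Working it through.** **1. Table 3 is consistent with itself.** Mean: (492 × 56.9 + 617 × 55.1)/1109 = 55.90. Combining within-sex and between-sex variance gives an SD of 6.39, against the printed 55.9 and 6.5. The age figures can be used as they stand.

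**2. Controls under 40, assuming normality.** z = (40 − 55.9)/6.5 = −2.45; Φ(z) = 0.0072; 0.0072 × 1109 ≈ 8.
- By sex: men Φ((40 − 56.9)/6.5) = 0.0047, × 492 = 2.3; women Φ((40 − 55.1)/6.2) = 0.0074, × 617 = 4.6; together about 7.
- Other cut-offs, same method: under 35 about 0.7 people, under 45 about 52, under 50 about 202.

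**3. Other age shapes with the same mean and SD.**

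| Shape | Controls under 40 |
|---|---|
| Normal | 7–8 |
| Heavy-tailed (scaled t, 4–10 df) | 12–14 |
| Left-skewed (Pearson III, skew −0.5 / −1) | 17 / 25 |
| Right-skewed (Pearson III, skew +0.5) | about 1 |
| Distribution-free ceiling, 1/(1 + z²) = 14.3% | 159 |

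The ceiling needs an extreme two-point age distribution and is not realistic. A working range is roughly 7 to 25.

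**4. Young IBD patients who could be matched.** The IBD age distribution is not in the shown text, so the share under 40 is an assumption. For 10% to 50% of 300 patients, that is 30 to 150 people. With 8 young controls used 1:1, 8/30 = 27% down to 8/150 = 5% could be matched. With 25 controls, 25/30 = 83% down to 25/150 = 17%.

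**5. Comparator events under 40.** At the lower planning rate of 1% per year (section 2.5), 8 controls yield 8 × (1 − e^−0.02) = 0.16 expected events in 2 years and 8 × (1 − e^−0.04) = 0.31 in 4 years. With 25 controls the 4-year figure is 25 × 0.0392 = 0.98. So at most about one control event would be expected.

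**6. What a loss of pairs does to the stated power.** First the plan's own figure: 1% per year, HR 2.5, 4 years, 300 per group. The proportions are 1 − e^−0.04 = 0.0392 and 1 − e^−0.10 = 0.0952, so Cohen's h = 2·asin√0.0952 − 2·asin√0.0392 = 0.2285. Power = Φ(h√(n/2) − 1.96) = 79.9%, against the stated 80% (two-sided 5% assumed). With the same formula and fewer pairs:

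| Pairs | Share dropped (assumption) | Power |
|---|---|---|
| 300 | 0% | 80% |
| 270 | 10% | 76% |
| 225 | 25% | 68% |
| 150 | 50% | 51% |

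This holds the event rate at 1%. If the patients dropped are the young ones, the remaining rate may be higher and the loss of power smaller.

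**The case against.** **The factor is a modest aim.** It is the last secondary objective and is worded as possible. The Discussion says the authors aim to propose it, and no under-40 stratum or age-specific factor is planned. The parallel cited is the single multiplier of 1.5 in rheumatoid arthritis. This stands. A reader might infer that the study's main product is an under-40 factor and that the factor cannot be estimated at all. The documents do not support that: one overall factor could be fitted where the ages overlap. What remains is that its use below 40 would be extrapolation.

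**The analysis has safeguards.** Section 2.5 checks balance by standardized mean differences (below 0.1 is good) and adjusts the Cox model for confounders. This stands in part. A gross mismatch would show, and adjustment would reduce bias in the hazard ratio. But neither step creates overlap, the baseline comparison is by unadjusted two-group tests, and no rule says what follows a failed check. A difference in means can also miss the problem: with IBD ages of 55 ± 12 (assumption), 10.6% (about 32 of 300) are under 40, yet the SMD for age is 0.9/√((12² + 6.5²)/2) = 0.09.

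**Bias is not certain.** A reader might infer that both comparisons will be biased. The documents support this only if matches carry no age limit. If young patients are dropped, the result is a narrower population, not this bias.

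**The scale is unknown.** The remark on younger adults describes IBD patients in general, and this cohort's ages are in Supplementary Table S1, which is not shown. The full protocol may also set age limits. This stands, so no figure for unmatched patients can be given beyond the assumed range.

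**National rates could stand in for young controls.** The article attributes a 1% to 5% annual range to national statistics. It shows no rates by age and sex, and none for its broad MACE definition under 40, so it cannot be taken that such a comparator is available.

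**Conclusion.** The point holds in this form. All controls come from a closed pool with about 8 of 1109 people under 40 under normality, and roughly 7 to 25 across the plausible shapes. Age matching will therefore either exclude most young IBD patients or, without an age limit on matches, pair them with older controls and make IBD look safer in the baseline-risk and MACE comparisons. A correction factor used under 40 would be extrapolated from older ages, with no more than about one expected control event behind it in that group at 1% per year over 4 years.

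This rests on the control ages having no extreme shape, and on the IBD cohort including an appreciable number of young adults, as the article's own description of IBD suggests. It does not rest on any particular share under 40. It matters because the primary objective depends on the age match, and analysis choices cannot add young people to a cohort that is already complete.

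**What to change.** 1. Report the age range and distribution of both cohorts, by sex, and the range that they share.
2. Match on sex and within an age caliper fixed before outcomes are examined.
3. Restrict the IBD–control comparisons (baseline risk, MACE and correction factor) to the shared age range. Keep unmatched younger patients in the within-IBD analyses (omics, disease activity, therapy).
4. Remove the statements in the Abstract and Discussion that the factor will serve under-40s, or say plainly that such use is an extrapolation without supporting data from this study.
5. Restate the expected number of matched pairs, and the power if fewer than 300 result.

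The cost is a change of wording in the protocol and analysis plan, a smaller matched comparison and a narrower claim. If the under-40 claim is to be kept as a finding, it needs an additional source of younger non-IBD controls, which is a larger change.
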